#### Data analysis

The analysis will be performed by intention to treat, and stratified for center and severity of prolapse. Patient characteristics will be summarized using descriptive statistics for continuous variables (mean ± standard deviation, minimum, maximum and sample size) and frequency tables for categorical variables (numbers and percentages).Statistical analysis of the data will be conducted at 12 and 60 months follow-up.

Surgical success of the apical compartment at 1 and 5 years follow-up in both study groups will be considered as the primary outcome. Success is defined as position of the cervix at or above the mid-vagina (C < -TVL/2), no symptoms (defined as no symptoms of vaginal bulging and protrusion on the validated questionnaire) and no reoperation or pessary use for recurrent apical prolapse. Failure in one of these areas will constitute a failure. Non-inferiority of laparoscopic sacrohysteropexy to vaginal sacrospinous hysteropexy will be concluded if the 95% confidence interval (CI) does not exceed the non-inferiority margin of 10% (Figure 2, scenario B). If the whole 95% CI exceeds the non-inferiority margin of 10%, the laparoscopic sacrohysteropexy will be considered to be inferior (scenario C). If the 95% CI for the difference in surgical success rates lies left from zero, it can be concluded that there is evidence of superiority of laparoscopic sacrohysteropexy over vaginal sacrospinous hysteropexy (scenario A) [31, 32].

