**Methods:**

The LAVA trial is a randomized controlled multicenter non-inferiority trial. The study compares laparoscopic sacrohysteropexy with vaginal sacrospinous hysteropexy in women with uterine prolapse stage 2 or higher. The primary outcome of this study is surgical success of the apical compartment at 1 and 5 years follow-up. Secondary outcomes are subjective improvement on urogenital symptoms and quality of life (assessed by disease-specific and general quality of life questionnaires), complications following surgery, hospital stay, post-operative recovery, sexual functioning and costs-effectiveness. Evaluation will take place pre-operatively, and 6 weeks, 6 months, 12 months and annually till 60 months after surgery. Validated questionnaires will be used.

Analysis will be performed according to the intention to treat principle. Based on comparable recurrence rates of 3% and a non-inferiority margin of 10%, 62 patients are needed in each arm to prove the hypothesis with a 95% confidence interval.

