### Statistical analysis

#### Sample size and power calculations

Sample size calculation was performed using Sample Power 2.0 (SPSS inc. Chicago, IL, USA). The aim of the study is to clarify whether laparoscopic sacrohysteropexy and vaginal sacrospinous hysteropexy do not differ significantly in surgical success rates of the apical compartment. We aim to demonstrate non-inferiority of the laparoscopic sacrohysteropexy at both 1 and 5 year (i.e. two tests on the primary endpoint will be performed). Two groups of 55 patients will be included to yield a 80% power for a non-inferiority margin of 10% assuming a recurrence rate of prolapse at the apical compartment of 3%. Taking into account 10% attrition, a number of 62 patients will be included in each study arm. This dropout can be expected when patients, after randomization, are unhappy with their allocated treatment and choose to end their participation in the study or due to incomplete or lost data. A total number of 124 women will be included in this study.

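### With 55 evaluable patients per arm, the stated 80% power and the 95% confidence interval rule cannot both hold: an interval that keeps its level gives about 65%

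*Protocol article*

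**What the plan says.** The article's section on sample size and power calculations states: "Two groups of 55 patients will be included to yield a 80% power for a non-inferiority margin of 10" percent, "assuming a recurrence rate of prolapse at the apical compartment of 3" percent. It then adds an allowance for dropout: "Taking into account 10% attrition, a number of 62 patients will be included in each study arm". It names the software but neither the formula nor the significance level. It also says that the endpoint is tested at 1 year and at 5 years ("i.e. two tests on the primary endpoint will be performed").

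The Data analysis section sets the decision rule: non-inferiority "will be concluded if the 95% confidence interval (CI) does not exceed the non-inferiority margin of 10" percent. The Methods paragraph of the abstract uses the same confidence level for the sizing: "62 patients are needed in each arm to prove the hypothesis with a 95% confidence interval". Neither place says which type of interval for a difference in proportions is meant.

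**The concern.** A two-sided 95% interval compared with a margin on one side is a one-sided 2.5% test. The power claim therefore has to hold at that error rate. At 3% failures the expected count is below two per arm, where large-sample formulas for a difference in proportions are unreliable and one more failure can change the conclusion.

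Two things are at stake. If the interval keeps its level, a laparoscopic procedure that truly matches the vaginal one would fail to show non-inferiority about one time in three, where the article implies one in five. If an interval that is too narrow is used, a procedure with 10 points more failures would pass more often than the 95% level implies. The Discussion asks for a sufficiently powered trial and makes the secondary outcomes decisive once non-inferiority is found, so both errors bear on how the trial will be used.

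**Working it through.** **Inputs.** From the sample size section: 3% failures (taken as equal in both arms, as the abstract's comparable rates imply), margin 0.10, 55 evaluable per arm, 10% attrition, 62 randomised per arm. From Data analysis: two-sided 95% interval, so one-sided 2.5%. Every power or error figure below is for one test at one time point.

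**1. The plan's own figures.** Attrition: 55 / 0.90 = 61.1, so 62, which agrees. For the 55, the unpooled normal formula is n = (z₁₋α + z₀.₈₀)² × 2 × 0.03 × 0.97 / 0.10²:
- one-sided 2.5%: (1.960 + 0.842)² × 5.82 = 45.7, so 46 (65 with continuity correction)
- one-sided 1.25%: (2.241 + 0.842)² × 5.82 = 55.3, so 56
- one-sided 5%: (1.645 + 0.842)² × 5.82 = 36.0, so 36 (55 with continuity correction)

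Thus 55 can be reached in more than one way, and not by this formula at the 2.5% of the decision rule.

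**2. Event counts.** Expected failures per arm are 55 × 0.03 = 1.65. An arm has none with probability 0.97⁵⁵ = 0.187.

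**3. Decision limits at 55 per arm.** The Wald rule is p₁ − p₂ + 1.96 × √[p₁(1−p₁)/55 + p₂(1−p₂)/55] < 0.10. The score rule puts in the variance the rates that best fit the data when the difference is exactly 0.10. Example, 2 laparoscopic and 0 vaginal failures:
- Wald upper limit: 0.0364 + 1.96 × 0.0252 = 0.0858. Non-inferior.
- Score: restricted rates 0.10 and 0, standard error √(0.09/55) = 0.0405, z = (0.0364 − 0.10)/0.0405 = −1.57, not below −1.96. Not shown.

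Largest laparoscopic failure count still declared non-inferior:

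| Vaginal failures | 0 | 1 | 2 | 3 | 4 | 5 |
|---|---|---|---|---|---|---|
| Wald 95% | 2 | 2 | 3 | 3 | 4 | 4 |
| Score or Newcombe 95% | 1 | 1 | 2 | 2 | 3 | 4 |

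**4. Power at 3% versus 3%.** Binomial(55, 0.03) gives P(0) to P(5) = 0.187, 0.319, 0.266, 0.145, 0.058, 0.018, and cumulative probabilities up to 1, 2, 3 and 4 failures of 0.506, 0.772, 0.917 and 0.976. Power is the sum, over vaginal counts, of the probability of that count times the cumulative probability up to its limit.
- Score or Newcombe: 0.095 + 0.161 + 0.205 + 0.112 + 0.054 + 0.018 = 0.645. Vaginal counts above 5 add 0.006, giving **65.1%**.
- Wald: 0.145 + 0.246 + 0.244 + 0.133 + 0.057 + 0.018 = 0.843. With the same 0.006, **84.9%** (from unrounded terms).

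**5. False non-inferiority at 13% versus 3%.** The same sum with the laparoscopic rate at 13% gives 1.8% for score or Newcombe and 4.8% for Wald, against a nominal 2.5%.

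**6. Could another method reach 80%?** A linear programme chose the rejection region that maximises power at 3%/3%, subject to error of at most 2.5% at all margin points checked (vaginal rates 0 to 30%). The maximum is 71.4% at 55 per arm and 77.2% at 62.

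**7. If all 62 per arm are evaluable.** Score or Newcombe 73.1%; Wald 88.2% with 4.6% error. Enumeration puts 80% for a score or Newcombe interval at about 74 to 75 evaluable per arm.

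**8. One-sided 5%.** A score test at this level has 79.9% power at 55 per arm, with 4.7% error at 13% versus 3%.

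**The case against.** The strongest reply is that the article condenses a longer protocol and the statistical analysis plan is not shown. The interval method may be fixed there, so its absence here is no fault, and the decision rule itself is standard. That stands, and the missing method is not the point. The bound in step 6 is: whatever method the unseen plan names, 80% power at 55 per arm is out of reach if the error is held at 2.5%.

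A reader might infer more, and the documents do not support it:
- That 55 came from the Wald formula. The article names only software. At one-sided 2.5% that formula gives 46. It comes near 55 only with alpha split over the two tests, which is nowhere stated. A one-sided 5% calculation fits at least as well.
- That the trial will use a Wald interval. The article adopts no interval type, so the 4.8% error is a consequence only if Wald is chosen.
- That the design delivers neither its power nor its error rate. It is a trade-off: Wald exceeds 80% power and the score interval holds the error. The two cannot be had together.
- That power should be judged with 97.5% intervals because there are two tests. The stated rule is a 95% interval.

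It is also fair to say that 65% is not the ceiling for a valid test (71.4% is). Nor is Newcombe strictly conservative: its error at 55 per arm reaches 2.7% at a vaginal failure rate of about 15%. Neither remark restores 80%.

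**Conclusion.** The point holds as an error in a stated figure. With 55 evaluable per arm, 3% failures in both arms, a 10-point margin and a 95% interval, power is about 65% with a score or Newcombe interval and at most about 71% with any test of size 2.5%. If nobody is lost, the figures are about 73% and 77%. The shortfall from 80% is therefore about 15 points at the planned evaluable number, and at least 9 whatever the method.

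This takes the 3% rate as given and assumes independent binomial counts and an unstratified analysis. The power shortfall is firm. Its cause is not: a mismatch between the alpha used for sizing and the 95% interval used for the decision is possible, but the document does not settle it.

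**What to change.** In the sample size section, state the formula and alpha behind 55. Restate the power as about 65% with 55 evaluable per arm, and about 73% if all 62 are evaluable, at 3% failures and a 95% interval. Bring the sizing sentence in the abstract into line.

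In Data analysis, specify an interval that holds its level with few events (Miettinen-Nurminen score or Newcombe) rather than Wald, and do so before outcomes are seen. The choice matters: at vaginal failure counts of 0 to 4, the limit differs by one patient between Wald and these methods.

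The analysis is to be stratified by center and prolapse stage. Six hospitals and three stages make up to 18 strata, with about 2 × 1.65 = 3.3 failures expected in total. The 65% and 73% do not carry over to a stratified interval, so check its power and error by simulation before adopting it.

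The cost is a less favourable stated power, one sentence on method and a short simulation if a stratified interval is wanted. It needs no extra patients or data.

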**Figure 2 Fig2:**
[figure not shown]
**Interpreting results of non-inferiority trials.** Δ stands for the non-inferiority margin. The results of a non-inferiority trial can conclude superiority **(A)** as the 95% confidence interval (CI) lies left from zero **(A)**, non-inferiority as the 95% CI does not exceed Δ **(B)** and inferiority as the 95% exceed Δ **(C)**. If the 95% CI included Δ, the results are inconclusive **(D)**.

### Ethics

The study is conducted in accordance with the principles of the Declaration of Helsinki. The LAVA trial has been approved by the Medical Ethical Committee of the Isala Klinieken Zwolle (METC 13/0320) and the local Ethical Committees of the participating centers. Prior to randomization, informed consent will be obtained.

## Discussion

In several studies it has been shown that uterine suspension in case of uterine descent is a safe and effective procedure compared to hysterectomy [11, 13–15, 18]. To our knowledge, a study that compares vaginal sacrospinous hysteropexy with laparoscopic sacrohysteropexy for the treatment of uterine descent has not been performed yet. It is unclear which treatment option gives the best anatomical outcome and the highest patient satisfaction. Therefore, a sufficiently powered randomized controlled trial with long-term follow-up is required to provide evidence based decisions on the preferred treatment. If non-inferiority in surgical success is found, the comparison of the secondary outcomes will be essential in selecting the preferred strategy.
